### Screening, recruitment and randomization

All RTR patients are screened for eligibility during the post-transplantation recovery period, so within 7–10 days after surgery, by the nephrologist. Eligible RTR are invited to participate, informed about the study protocol and if agreed are asked to participate and sign written informed consent. In case of non-Dutch or non-English speaking patients, interpreters are used.

In total, 219 participants (73 per group) will be recruited. The sample size is based on the expected improvement on the physical functioning scale of quality of life of 13.8 points in the intervention group and 8.8 points in usual care (α=0.05, β= 0.80, SD = 11.0) [26]. A difference of 5.0 points between the standard effect is considered a relevant effect. This results in a required number of 57 RTR per group. Taking into account a potential dropout rate of 15% and a correction for heterogeneity between centers of 10%, this results in a total required number of 73 RTR per group (*N* = 219 in total). Randomization to one of the three arms is computerized using the ‘PROC SURVEYSELECT’ function in the software program SAS (Cary, North Carolina, USA). It is performed by an independent data management company hosting the data entry facility, who are not involved in conducting the study itself (Nefrovisie foundation, Utrecht, the Netherlands). Participants are randomized by block randomization in groups of 6–9 for rehabilitation centers and in groups of 3 for physiotherapy practices.

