### Statistical analyses

Short term differences between groups will be tested using students T-test or linear regression, and long term differences will be tested using General Linear Mixed models. Time will be analyzed for exercise intervention (phase 1) and maintenance period (phase 2). Centers will be taken into account as random factor. Intention to treat principle will be applied in primary analyses. Per protocol analysis will be based on completion of the exercise training sessions, and attendance of dietary counseling sessions. Stratified analysis are foreseen for time after transplantation, socio-economic status and immunosuppressive regime. Furthermore, potential preset determinants of intervention outcome will be evaluated in a GLM model: gender, age, coping style, fear of movement, work participation and clinical factors.

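### The 57 per group gives 80% power only on a basis the protocol does not declare; an unadjusted comparison of one intervention arm with usual care has about 67 to 78%

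*Protocol article*

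**What the plan says.** All the inputs stand in the protocol article under Screening, recruitment and randomization. The expected improvement in SF-36 physical functioning is "13.8 points in the intervention group and 8.8 points in usual care". The relevance threshold follows: "A difference of 5.0 points between the standard effect is considered a relevant effect". The remaining inputs are "α=0.05, β= 0.80, SD = 11.0", and the result is "This results in a required number of 57 RTR per group". After "a potential dropout rate of 15% and a correction for heterogeneity between centers of 10" per cent, "this results in a total required number of 73 RTR per group", which is 219 in three equal arms.

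The effect assumption refers to a single intervention group, but the trial has two. The Abstract's aim and the opening of Methods/design set usual care against exercise and against exercise plus diet as separate arms, and the Health economic analysis section also compares each intervention with usual care. Under Statistical analyses, "Short term differences between groups will be tested using students T-test or linear regression", and mixed models are named for the long term. No section says that the two exercise arms are pooled for the primary outcome, and none gives a baseline correlation or variance reduction behind the sample size.

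**The concern.** A reader will take the 80% power to apply to each intervention against usual care, because those are the comparisons that the aims describe. On the printed inputs, the standard two-sample calculation for such a comparison gives a clearly larger number than 57.

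If the 57 was derived for something else, the power for the separate-arm comparisons is lower than the text implies. A true 5-point benefit of one programme would then be missed about one time in three, not one in five. A non-significant result on the primary outcome could be read as evidence against a relevant effect when the trial was not sized to support that conclusion.

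The printed β of 0.80 adds to the uncertainty: taken literally, it means 20% power.

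**Working it through.** **Inputs** (Screening, recruitment and randomization): difference δ = 13.8 − 8.8 = 5.0; SD σ = 11.0; α = 0.05, sidedness not stated; 0.80 read as power. Read literally as β, it would give 2 × (1.960 − 0.842)² × (11/5)² = 12.1 per group, so it is a labelling slip.

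**Reproducing the plan's 57.** With (1.960 + 0.842)² = 7.849 and (11/5)² = 4.84:

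- Both exercise arms pooled against usual care, 2:1, two-sided: (1 + 1/2) × 7.849 × 4.84 = 56.98, so 57 per arm (57.6 by t-test).
- One arm against usual care with a 25% variance reduction, for example baseline adjustment with correlation 0.5: 2 × 7.849 × 4.84 × (1 − 0.5²) = 75.98 × 0.75 = 56.98.

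The two routes give the same number, so the 57 cannot show which was used.

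**Other bases tried, none giving 57:**

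- One arm against usual care, two-sided, unadjusted: 2 × 7.849 × 4.84 = 75.98, so 76 per group (77 by t-test).
- The same, one-sided: 60 (61 by t-test).
- Pooled 2:1, one-sided: 45.
- Three-group ANOVA with means 8.8, 13.8 and 13.8: 71.

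**From 57 to 73.** 57 × 1.15 × 1.10 = 72.1 and 57 / 0.85 × 1.10 = 73.8. The stated 73 is consistent with these and is not in question.

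**Power for one arm against usual care**, unadjusted, two-sided, δ = 5.0. Normal approximation: Φ(5 / (11 × √(2/n)) − 1.960). For n = 57: 5 / 2.0605 = 2.427; 2.427 − 1.960 = 0.467; Φ = 0.680.

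| Analysed per group | How reached | Normal | t-test |
|---|---|---|---|
| 56.4 | 73 × 0.85 / 1.10, both allowances | 67.5% | 66.7% |
| 57 | the plan's required number | 68.0% | 67.2% |
| 62 | 73 × 0.85, dropout only | 71.6% | 70.9% |
| 73 | no loss, no centre effect | 78.4% | 77.9% |

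**Pooled contrast**, 57 against 114: 80.0% (79.6% by t-test).

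**Difference detectable with 80% power** at the effective size: 2.802 × 11 × √(2/56.4) = 5.80 points, slightly more by t-test (5.82 to 5.85).

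**Scale of the gap.** With the plan's own allowances, 80% power for an unadjusted single-arm comparison would need between 76 × 1.15 × 1.10 = 96.1 (97) and 77 / 0.85 / 0.90 = 100.7 (101) per group.

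**The case against.** The strongest reply is that the 57 is not a miscalculation. It follows exactly from the printed inputs once both exercise arms are set against usual care, and some of the text fits that reading: the effect assumption speaks of one intervention group, the exercise programme is the same in both arms, and the Outcomes section defers the effectiveness of the diet component to 15 months. This stands. A reader might infer an arithmetic error, but the documents do not support that. What is missing is the declared contrast.

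A second reply is that the analysis need not be an unadjusted t-test. Linear regression is offered as the short-term alternative, mixed models are named for the long term, and the SF-36 is measured at four time points. Baseline adjustment with correlation 0.5 would restore 80% power to each separate-arm comparison. This stands too, so 67% is not an unconditional property of the trial: it assumes an unadjusted test and both allowances deducted. Even so, the article neither commits the primary outcome to an adjusted model nor gives a correlation.

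A third reply is that a condensed article may leave the basis of the calculation to the full protocol. That excuses brevity, but this article prints the inputs, the result and the comparisons, and as printed they do not fit together.

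Two further inferences go too far. The article claims no power for exercise plus diet against exercise alone, so that contrast cannot be said to fall short of a promise. It also specifies no division of α between comparisons, so no power figure should be based on one.

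**Conclusion.** The point holds as a mismatch between the basis of the sample size and the comparisons that the trial says it will make. For an unadjusted two-sided comparison of one intervention arm with usual care, 57 per group does not give 80% power at 5.0 points; 76 to 77 are needed. Power is about 67% after both of the plan's allowances, about 71% after dropout only, and 78% with all 73 analysed, so no scenario reaches 80%.

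These figures assume SD 11.0, two-sided α of 0.05 without multiplicity adjustment, and no gain from baseline or repeated measurements. If the 57 rests on pooling, the 80% is right for the pooled contrast but not for the separate arms. If it rests on baseline adjustment with correlation near 0.5, the 80% is right for each arm, provided that model is the primary analysis.

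**What to change.** Keep 219 participants and change the text.

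1. Replace the printed β with power = 0.80 (β = 0.20).
2. State, before any outcome data are seen, which contrast and analysis the 57 supports.
   - If pooled: make pooled exercise against usual care the primary contrast for SF-36 physical functioning, and report the power of the separate-arm comparisons as about 67 to 71%.
   - If baseline-adjusted: state the assumed correlation and make that adjusted model primary.
3. If neither basis applies, restate the power for each arm against usual care as about 67% (71% with dropout only), with 80% power at about 5.8 points.

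This costs wording and no extra patients. The downside is that the stated power for the separate-arm comparisons becomes less favourable unless a baseline-adjusted basis can be documented.

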### Setting and participants

Recruitment takes place in three Dutch hospitals with good geographical coverage, in the north (University Medical Center Groningen), west (Amsterdam Medical Center) and south (Maastricht University Medical Center) of The Netherlands. The exercise training is offered in rehabilitation centers or in local physiotherapy practices if there is no rehabilitation center within reasonable travel distance of the residence of the participant.

Delivery of the exercise training is standardised by providing protocols and the same exercise training protocol for all interventionists.

### Professionals

The interventionists of the participating centers all received personal instructions of exercise scientists on the protocols, the basic medicine of renal disease, and adverse effects of the immunosuppressive- and other medication. Furthermore, all interventionists participated in a mandatory kickoff meeting where the lifestyle counseling part of the intervention was explained and practiced, including the theoretical background (stages of change model and motivational interviewing). All participating rehabilitation centers and physiotherapy practices meet the following criteria: expertise in rehabilitation of cardiovascular or oncology patients; adequate training facilities; all the necessary fitness equipment for submaximal cycle ergometry and strength tests; and, for physiotherapy practices only, provide opportunities for participants to continue their fitness activities during the active follow-up.

Concerning the diet intervention, dieticians are required to meet the following selection criteria: experience in counseling renal patients or other patients with a serious chronic metabolic condition; educated and experienced in motivational interviewing; educated and experienced in Subjective Global Assessment of malnutrition. Lifestyle coaches had to fulfill the following selection criteria: experience in lifestyle counseling of renal patients or other patients with a serious chronic metabolic condition; educated and experienced in motivational interviewing. In most cases the lifestyle counseling is done by the physiotherapist who supervises the training.

A website dedicated to the study (in Dutch language) provides all protocols, explanations and hosts a data entry system (www.act-studie.nl).

### Usual care

Participants randomized to the usual care group receive standard post-transplant care as usual in the hospitals. Current standard nutrition care after kidney transplantation consists of 1–4 inpatient consultations by a renal dietitian during the inpatient stay (7–10 days), followed by 1 outpatient consultation. During inpatient consultations attention is paid to optimal nutritional intake, maintaining a stable body weight and muscle mass, or increasing body weight when needed. After a few months, during the outpatient follow-up, attention is paid to maintaining a stable body weight, or increasing or decreasing body weight when needed. When a participant has increased cholesterol, (un)saturated fat intake is discussed, and mono/disaccharides are discussed when a participant has increased HbA1c. Likewise, salt consumption is discussed in case of increased 24-h sodium excretion. Exercise or lifestyle counseling are not included in the standard post-transplant care in either of the participating hospitals. Participants randomized to the usual care group receive general advice to meet the standard Dutch exercise guidelines (30 min of moderate physical activity per day) and follow the Dutch Dietary guidelines.

### Exercise only intervention

The exercise intervention consists of two phases. The first phase is a 3-month exercise training program, followed by the second phase; a 12-month active follow-up with lifestyle counseling (Figure 2). Exercise training sessions are done in groups of 4–10 participants in the rehabilitation centers and with 1–6 participants in the physiotherapy centers.

The training program encompasses two exercise training sessions per week (21 exercise training sessions and 3 test sessions in total) and is focused on improving maximal muscle strength, local muscle endurance, and aerobic capacity. Each exercise training session consists of 30-min dynamic resistance training of all the major muscle groups (Additional file 1: Table S1) using resistance training machines, 30 min of aerobic training (cycle-ergometry and treadmill walking), and is concluded with a 30-min supervised sports activity or swimming, depending on the available facilities.

The dynamic resistance training includes both maximal strength training (relatively high load, fewer repetitions), and muscle endurance training (relatively low load, large number of repetitions).

Optimal resistance training load is determined using one-repetition maximum testing (1RM) for each participant. The content of the training program is in line with the American College of Sports Medicine guidelines exercise in healthy adults [27], and was previously shown to be effective in improving muscle strength and aerobic capacity in RTR [22]. The full resistance- and aerobic training program is shown in Additional files 1 and 2: Tables S1 and S2.

Maximal muscle strength (1RM) for all exercise machines (Additional file 1: Table S1) is assessed at baseline. For maximal muscle strength training, moderate loading is used (50–60% 1RM), for 2–3 sets of 8–10 repetitions. Higher loads are known to be more appropriate for maximal muscle strength, however 50–60% 1RM is used in our protocol as most participants are untrained, and RTR have increased risk of tendon ruptures. For local muscle endurance training a light-to-moderate load is used (25–35% 1RM), for 1–3 sets of 30 repetitions. All resistance exercise involved exercise machines, no free weights are used for safety reasons.

The load for the aerobic cycle training is determined based on the baseline symptom-limited graded maximal cycle ergometry test. Treadmill walking is performed at the load at which heart rate is similar to the heart rate during aerobic cycle-training. If the physiotherapists notice that a subject is training below or above the optimal intensity (e.g. in case a baseline exercise test is performed sub optimally), they are allowed to make slight adjustments to the participants’ exercise intensity.

#### Lifestyle counseling

During the active follow-up, participants are supported to continue sports activities and keep up daily physical activity by lifestyle coaches. A total of 5 lifestyle counseling consultations are scheduled during the entire exercise intervention and similar for the exercise + diet intervention, see next paragraph: at 6 weeks, 12 weeks, 16 weeks, 6 months, and at 15 months. The first two consultations are face-to-face and combined with the exercise training sessions. Consultations at 4 and 6 months are done face-to-face if possible, otherwise by phone. The final lifestyle counseling session is face-to-face together with the final test moment at 15 months. To optimize participant motivation, the lifestyle counseling is in line with the Self-Determination Theory, fostering the perceived autonomy, competence and relatedness [28–30]. Additionally, the Stages of Change model is applied, and readiness for change is assessed at the first 2 lifestyle counseling sessions to better tailor the content of the consultations to the participants' readiness to change their exercise and physical activity behavior [31]. During these lifestyle counseling sessions a motivational interviewing approach is used. During the lifestyle counseling participants receive several tools to stimulate a physically active lifestyle, including an information leaflet of the Dutch Kidney Foundation on exercise and physical activity after renal transplantation [32], a step counter to stimulate physical activity through self-monitoring, and finally, a hard-copy log book for educational and motivational purposes. The log book includes advice on exercise, finding an exercise buddy, setting personal goals, and tables to log one’s own exercise behavior.

### Exercise + diet intervention

The exercise training program in the exercise + diet intervention group is identical to that of the exercise intervention group, and additionally, participants receive dietary counseling. The dietary counseling runs throughout the entire 15 months of the study period and consists of a total of 12 counseling sessions with a renal dietician. The dietary counseling takes place in the hospital face-to-face. If this is not feasible some counseling sessions are done by phone. The dieticians are trained to use motivational interviewing techniques which they apply during the dietary counseling sessions.

Goals are set to improve nutrition status to preserve renal function, to prevent weight gain, type 2 diabetes, and hypercholesterolemia. These goals are set together with the participant to facilitate an autonomy supportive counseling climate [33]. A three-day food diary is used as input during the dietary consultations and for personal goal setting. Participants also receive a food logbook which contains information and exercises to help the participant set diet goals. During the dietary counseling sessions, special attention is given to salt intake, whole-wheat grains and fruit and vegetable intake, intake of saturated and unsaturated fat, and the use of sugar-rich products, sugar-sweetened beverages (soft drinks, sweetened dairy drinks and fruit juices) and preventing overeating. In addition, participants are reminded of their physical activity goals, and the importance of protein intake for maintaining and increasing muscle mass. In case of disease after transplantation, for example infections, the dietician assists the patient in maintaining an energy- and protein-rich diet to prevent further deterioration or decline in muscle mass.

Dietary counseling session 9 (of total 12) is a group meeting for which the participants are encouraged to bring significant others such as their partner or other supportive family members. The dietary counseling is in line with the 2006 Guidelines for a Healthy Diet by the Dutch Food and Nutrition Council [34], supplemented with diet guidelines for RTR [35] and diet guidelines for the prevention of type 2 diabetes [36] and cardiovascular risk [37].

### Immunosuppressive medication regimen

All participants receive standard immunosuppressive treatment. In the UMCG this consists of induction therapy with methylprednisolone (40 mg) and basiliximab (20 mg) on day 1 and at day 4 post-operation. This is followed by a maintenance immunosuppressive regimen of tacrolimus, mycophenolate mofetil and prednisolone, tapered to a maintenance dose of 5-10 mg per day. Standard immunosuppressive treatment in the MUMC consists of no induction therapy, methylprednisolone 125 mg per day intravenous during the first 48 h, starting perioperative, followed by a maintenance immunosuppressive regimen of mycofenolate mofetil 2dd 1000 mg, after two weeks 2dd 500 mg and tacrolimus .

Standard immunosuppressive treatment in the AMC consisted of induction therapy CD25 mAB intravenous prior to transplantation, and at day 4 post-operation. Methyl prednisolone 2 × 50 mg intravenous during the first 48 h, starting perioperative. This is followed by a maintenance immunosuppressive regimen of tacrolimus, mycophenolate mofetil and prednisolone tapered to a dose of 5–10 mg per day.

### Outcomes

The primary outcome is the subdomain physical functioning of quality of life of the SF-36. Secondary outcomes include other evaluations of quality of life (SF-36, KDQOL-SF, EQ-5D), muscle strength (Additional file 1: Table S1), aerobic capacity, physical activity, gain in adiposity (body fat percentage by bio-electrical impedance assessment, BMI, waist circumference), and cardiometabolic risk factors (blood pressure, lipids, glucose metabolism). Furthermore, data on renal function, medical history, medication, psychosocial factors (motivation, kinesiophobia, coping style), nutrition knowledge, nutrition intake, nutrition status, fatigue, work participation, process evaluation and cost-effectiveness are collected. Effectiveness of the diet intervention will be determined at 15 months. To study barriers and success factors regarding lifestyle counseling in RTR, data are gathered on psychological factors including motivation, kinesiophobia, and coping style. A comprehensive overview of the measurements in the ACT trial is shown in Table 1.

**Table 1 Tab1:** Overview of measurements in the ACT trial

Outcome	Method	Time points
Quality of life		T0, T3, T6, T15
Physical functioning	SF-36 PF subscale [72, 73]	
Other subdomains and total	SF-36 [72, 73]	
Renal specific	KDQOL-SF [39]	
General	EQ-5D [69]	
Physical function		
Aerobic capacity	VO_2_peak ergometer test [74]	T0, T3, T6, T15
	Sub-maximal ergometer test	T0, T3, T6, T15
Muscle strength	1RM tests for leg extension, leg curl, chest press, close-grip pull-down	T0, T3, T6, T15
Balance and mobility	Short Physical Performance Battery [41]	T0, T15
Physical activity level	Baecke questionnaire [42]	T0, T3, T6, T15
	Step counter (Yamax SW200) [75]	T0, T3, T6, T15
Body composition		
Weight, Height, WC, HC	WHO guidelines [76]	T0, T3, T6, T15
Nutritional status (undernutrition)	SGA [77]	T0, T15
Body fat percentage	BIA (Biostat Quadscan 4000, Douglas, Isle of Man)	T0, T3, T6, T15
Muscle mass	BIA (Biostat Quadscan 4000, Douglas, Isle of Man)	T0, T3, T6, T15
	24-h creatine excretion [44, 78]	T0, T3, T6, T15
Cardiometabolic risk factors		
Blood pressure	(Speidel & Keller Maxi Stabil 3)	T0, T3, T6, T15
Blood lipids	TG, TC, HDL-C, LDL-C in fasting serum levels (Cholesterol oxidase-phenol aminophenazone method, MEGA AU 510; Merck Diagnostica, Darmstadt, Germany)	T0, T3, T6, T15
Glucose metabolism		
Insulin resistance	HOMA-IR (fasting glucose, insulin)	T0, T3, T15 (all)
